## Discussion

When designing the study protocol we had to make a number of considerations, which may lead to the following strengths and weaknesses:

### Strengths

According to our knowledge this is the first prospective randomized controlled trial evaluating whether multidisciplinary nutritional support is cost-effective in a randomized design. This study is apparently also the first study of multidisciplinary nutritional support among home-care clients.

Both are highly relevant, respectively, for a research point of view and for the health economy aspect.

The methods used by the multidisciplinary team and most of the planned outcome measurements have been used in other studies and proven feasible among the target population for the present study. Also the RAI-NH version 2.0 and the RAI-HC version 2.0 has been used in former research studies among, respectively, Danish nursing home residents and home-care clients (e.g.
[5, 12]). This gives us the opportunity to compare our results with the results of the former studies and is also why it has been decided to use these older versions of the Resident Instrument Assessment, instead of the recently developed newer versions.

We have chosen not to use strict exclusion criteria, even though they are suffering from a variety of chronic diseases and have different living conditions. Furthermore, the involved multidisciplinary team, registered dieticians, physiotherapist and occupational therapist are already today available in the Danish municipalities. Finally there is a lot of focus on rehabilitation which also involves a multidisciplinary approach – even though this is often without a nutritional support. All in all, this means that if the results of a broad study like this one are positive, it justifies wide implementation in the municipalities.

### Weaknesses

We have chosen to include participants with 2 points in EVS, instead of using e.g. the Mini Nutritional Assessment (MNA), which might limit the comparability with other studies. The reason for choosing EVS is that this tool, in contrast to e.g. the MNA is developed and validated in order to identify older adults in home-care and nursing home, who could benefit from nutritional support. However, whether this is actually true has never been examined before
[10].

The participants included in the study should be able to complete the planned tests and to give informed consent. These criteria might exclude demented and functionally impaired persons and hence reduce the representativeness of our findings.

Furthermore, according to our knowledge, there have only been performed a few randomized controlled studies of nutritional support among home-care clients and none using a multidisciplinary approach.

Finally the EQ-5D-3L has apparently not been used in this population before. Hence our expectations about feasibility of recruitment and sample size assessment are based on relatively few published data, primarily among nursing home residents. However we expect that the home-care population is less frail than the nursing home population and therefore may be more willing to participate.

In relation to this, we have decided to use cluster randomization to avoid contamination. Hence the estimated sample may be too small to detect a significant difference
[25]. Due to limited time and resources it is not possible to increase the number of clusters. To try to compensate for this we aim to include statistical analysis of the percentage of individuals in the different clusters that benefits.

We could have decided to use the Short Physical Performance Battery (SPPB) for the functional assessment. SPPB measures chair rise, balance and gait speed. However instead we decided to use methods which we had experience working with from former studies, and which gives some of the same information as the SPPB, i.e. 30 seconds chair-stand and RAI.

We have decided to use quality of life as our primary outcome. Another relevant outcome measure could have been ADL, especially since former studies have shown that older adults in respectively, nursing homes and home-care, who are undernourished, need more assistance with ADL than older adults who are in good nutritional status and due to that, may add to the substantial and costly burden of care
[3, 5, 6]. Apparently it seems difficult to convey improvement in ADL to cost, since the price is unknown.

Also it could have been relevant to consider the cost of hospital admissions, visits of general practitioners, or moving to nursing homes. However our sample size lacks power in order to be able to detect a significant difference in these outcomes.

It could have been interesting to evaluate the co-morbidities of the participants since pathologies may interfere with food intake and nutritional status change. Unfortunately we do not have access to this information.

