### Feasibility of recruitment and sample size

Unpublished results have shown that around 25% of nursing home residents will achieve 2 points in the EVS. According to our knowledge no nutritional support studies among nursing home residents and home-care clients have used Euroquol-5D-3L. However in a study of multidisciplinary nutritional support among another frail group of older adults, patients with hip fractures, Hoekstra and co-workers
[15] used this measure and found a significant difference between intervention and control group in the Euroquol-5D-3L follow-up score of 0.145 (p = 0.004). Hence, with a statistical significance level of 0.05 and a power of 80% two groups of 65 older adults is calculated to be sufficient. The above mentioned unpublished study found that it was possible to screen 600 nursing home residents during an 8 weeks period.

Taking into account an expected loss to follow up of 10% during the 11 weeks of intervention based on a former multidisciplinary study among nursing home residents
[12], and estimating equal findings among home-care clients, we aim to include a total of 145 older adults with 2 points in EVS. We therefore need to screen about 600. This number could probably be reached in approximately 8 weeks.

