### Control group

Before start of the intervention a nutrition education program will be performed educating selected staff members from the participating home-care and nursing homes to take the role as nutrition coordinator. The education of the nutrition coordinator includes three whole-day courses plus train-the-trainer sessions with other staff members (based on
[13]) and local study circles in-between (based on
[17]). These nutrition coordinators will be active in both the control and the intervention group. Also, in both groups standard interventions from physiotherapist, registered dietician and occupational therapist requested through the municipality’s normal assessment and referral system will be maintained.

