#### Fall incidents, hospital admissions, rehabilitation stay, moving to nursing homes, and mortality (t = 11)

These information’s will be gathered by means of data from the RAI-NH version 2.0 and RAI-HC version 2.0 assessments and the municipality care register system.

For each participant the same trained nurse will collect RAI-NH version 2.0 and RAI-HC version 2.0 data at t = 0 and t = 11.

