#### Economic evaluation (t = 11)

At the end of the trial, having received the data, an economic evaluation of the intervention will be carried out. This evaluation will take the form of a cost-effectiveness study, in which the intervention with its different forms of nutritional support is modeled as a decision tree, so that the citizen is followed through the intervention, costs and effects being assigned to its different varieties.

The effects of the intervention will be measured both in terms of changed body weight and as change in health-related quality of life, measured in QALYs on the basis of the EQ-5D-3L measurements. Time used for the different tasks will be registered and used in the calculations. The cost of the intervention includes cost of screening, cost of the multidisciplinary nutritional support and cost of training the staff for the specific tasks specified by the intervention. The results will be compared to other interventions in healthcare, and the uncertainties in the assessments will be illustrated by suitable sensitivity analyses.

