## Conclusion

In this study we will evaluate in a randomized controlled trial whether multidisciplinary nutritional support is cost-effective, in undernourished older adults in home-care and nursing home. According to our knowledge no other studies has assessed this ad hence the study will contribute to important research. If the expected higher costs are negligible compared with increased quality of life and the cost-savings this can potentially generate, the results might influence common practice positively.

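### The costing sets aside hospital and nursing-home costs because a difference would not be significant, and counts screening that both arms receive as a cost of the intervention

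*Protocol article*

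**What the plan says.** **The question.** The aim at the end of the Background is to assess cost-effectiveness. The Background expects higher delivery costs that may prove small beside better quality of life and savings. The Conclusion makes the result depend on the same balance: "If the expected higher costs are negligible compared with increased quality of life and the cost-savings this can potentially generate".

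**The costs named.** Economic evaluation (t = 11): "The cost of the intervention includes cost of screening, cost of the multidisciplinary nutritional support and cost of training the staff". The sentence then ties the training to duties that the intervention itself creates. The section has no line for admissions, rehabilitation stays, nursing-home moves or social services.

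**The costs set aside.** The Weaknesses section says that the cost of hospital admissions, general practitioner visits and nursing-home moves could have been relevant, and continues: "However our sample size lacks power in order to be able to detect a significant difference in these outcomes".

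**The data collected.** Design and Outcome parameters list admissions, rehabilitation stays, moves to nursing homes and use of social services as outcomes compared between the arms. The source for the events includes "RAI-HC version 2.0 assessments and the municipality care register system". Procedure for baseline assessment adds hours and type of home help and home nursing, collected again at the end of the intervention.

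**What the arms share.** Under Design and Nutritional status, 2 points on the EVS screen is the entry criterion for everyone. On the trained coordinators, the Control group section says: "These nutrition coordinators will be active in both the control and the intervention group". It also keeps ordinary referrals to the three professions in both groups.

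**The concern.** A cost-effectiveness analysis needs the mean difference in total cost between the arms, with its uncertainty. It does not need each component to differ significantly. Dropping a component because its p-value would be large amounts to fixing its increment at exactly zero with no uncertainty, which is a stronger claim than a wide interval around an estimate. The sensitivity analyses promised in the Economic evaluation section cannot show uncertainty in a cost that was never entered.

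The criterion is also applied unevenly. The Weaknesses section concedes that, because of the cluster design, the sample may be too small for a significant difference, yet the primary outcome is kept and will supply the QALYs.

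Screening raises the reverse problem. The effect is measured against a control arm that was screened too, so it contains no benefit of screening. Charging screening to the intervention sets a cost that both arms carry against an effect that they do not share.

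At stake is the trial's stated question: whether savings offset delivery costs cannot be read from an analysis in which the main sources of saving have no entry.

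**Working it through.** **1. The plan's own figures.** Feasibility of recruitment and sample size takes a difference in "Euroquol-5D-3L follow-up score of 0.145" and states that "with a statistical significance level of 0.05 and a power of 80% two groups of 65 older adults is calculated to be sufficient". No SD is given. Solving SD = 0.145 / [(1.960 + 0.842) × √(2/65)] gives 0.295 (two-sided), so 65 per group is consistent with the inputs but cannot be checked independently. Allowing for 10% loss, 130 / 0.90 = 144.4, rounded up to 145: the planned total reproduces, and this point does not affect it.

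**2. Is the lack of power true?** The document gives no event rates, so those below are assumptions. With 65 per arm, two-sided 0.05 and no allowance for clustering, power = Φ[(|p1 − p2| − 1.96 × SE0) / SE1], where SE0 uses the pooled proportion and SE1 the separate ones.

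| Assumed rates | Power |
|---|---|
| 10% v 5% | 19% |
| 20% v 10% | 36% |
| 20% v 15% | 11% |
| 30% v 20% | 26% |
| 30% v 15% | 54% |

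With six clusters, power would be lower. The premise is true; the step from low power to leaving out the cost does not follow.

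**3. Is screening incremental?** About 600 screens for 145 participants is 600 / 145 = 4.1 screens per participant. Charged to the intervention arm alone, taken as half of 145, it is 600 / 72.5 = 8.3 per intervention participant. Against this trial's control arm the increment is 0, because both arms enter through the same screen.

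**4. How far does a costing error move the ratio?** Inputs are the planning effect of 0.145 and measurement at 0 and 11 weeks.
- Gain present throughout: 0.145 × 11/52 = 0.0307 QALY.
- Gain building linearly from zero: 0.0307 / 2 = 0.0153 QALY.
- 100 euro per participant: 100 / 0.0307 ≈ 3,260 and 100 / 0.0153 ≈ 6,520 euro per QALY (unrounded QALYs used).
- 500 euro per participant: about 16,300 to 32,600 euro per QALY.

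The document gives no unit costs, so these figures are sensitivities and not estimates of the actual error.

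**The case against.** The strongest reply is one of context. The sentence in Weaknesses follows a discussion of alternatives to quality of life as the primary outcome, where low power is a proper reason. The cost sentence in the Economic evaluation section says *includes*, which is not a closed list, and a decision tree with costs and sensitivity analyses is promised. A journal article may also leave perspective, unit costs and the full cost list to a fuller plan. Finally, screening cost matters for a national roll-out, which the Background says is planned.

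Part of this stands. A reader might infer four stronger things that the document does not support:

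- **That the intervention can only cost more.** This holds for the three items named, but the list is not closed, and rehabilitation stays and social services are nowhere expressly excluded.
- **That training given to both arms is charged to the intervention.** The sentence limits the training to duties specified by the intervention, which need not mean the shared coordinator education. The text is unclear.
- **That the omitted costs approach 10,000 euro per participant.** The Background gives that figure as the extra cost of managing undernourished nursing-home residents, with no period. It is neither an intervention effect nor an 11-week saving.
- **That each 100 euro moves the ratio by 6,520 euro per QALY.** That is only the upper end of the range.

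The reply does not remove the core. The Weaknesses sentence concerns the cost of these events, and the reason it gives is significance. That is stated text, not a detail left to another document. The roll-out argument supports a separate scenario, since this trial has no unscreened arm.

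**Conclusion.** The point holds on two counts. First, lack of power is not a valid reason for setting aside the cost of admissions and nursing-home moves in a trial whose conclusion weighs savings, when the events are collected in both arms. Second, screening is counted as a cost of the intervention although its increment against the control arm is nil. Whether shared training is charged as well is an open question for the sponsor.

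The sensitivity of about 3,260 to 6,520 euro per QALY for each 100 euro per participant assumes that the full 0.145 is reached and that no gain is counted beyond week 11. A smaller gain makes the ratio more sensitive: half the effect doubles both figures. The direction of the net error cannot be stated, because leaving out savings and charging screening raise the ratio, while leaving out any added downstream cost lowers it. The primary EQ-5D comparison and the sample size are unaffected.

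**What to change.** 1. **Base case.** Apply unit costs in both arms to the collected admissions, rehabilitation stays, nursing-home moves and social-service use, together with team support and, where recorded, ordinary referrals. Report the incremental cost with an interval that reflects the clustering, whatever the p-values.
2. **Shared items.** Give EVS screening, and any training that both arms receive, zero increment in the within-trial comparison. Show them only in a separate, labelled roll-out scenario.
3. **Wording.** State the comparator and the cost perspective, and say which training the Economic evaluation section means. In Weaknesses, remove lack of power as a ground for omitting costs. Leave out general practitioner visits, giving as the reason that they are not listed as collected.

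**Cost.** Unit prices, some extra costing work and rewording. The event types are already collected, but the document does not mention lengths of stay, so these may have to be retrieved. The cost interval will be wider, and with six clusters it may be very wide; that is the uncertainty the trial actually has.

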## Conclusion

In this study we will evaluate in a randomized controlled trial whether multidisciplinary nutritional support is cost-effective, in undernourished older adults in home-care and nursing home. According to our knowledge no other studies has assessed this ad hence the study will contribute to important research. If the expected higher costs are negligible compared with increased quality of life and the cost-savings this can potentially generate, the results might influence common practice positively.
